# Aims and objectives

The primary objective of this pilot RCT study is to:

1. To evaluate feasibility (cost and practicability) and acceptability of an early psychiatric intervention in a post-ICU clinic.

Secondary Objectives are:

1. Assess the impact of early psychiatric assessment and provision of referral options on self-efficacy and rates of health service access for patients requiring psychological intervention post-ICU
2. Measure the change in symptom severity for anxiety, depression, and PTSD between presentation, and 6 months after presentation.
3. Measure the impact on work, income, and independence in activities of daily living (ADL)

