**Participants and sample calculation:**

Data will be collected from a sample of approximately 30 patients attending the Redcliffe ICU follow-up clinic over a 12-month period, with 15 randomised to the control and intervention arms respectively.

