**PICS Feature Measure Minimally Clinically Important Difference (MCID)**

Anxiety/Depression HADS* ≥ 2.5 points[17]

PTSD PCL-5 ≥ 10 points[18]

Physical Function EQ5D* ≥ 0.5 points[19]

*Collected as part of routine clinic practices

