## Statistical analysis

The demographics and results of the Baseline Outcome Measures Bundle will be described using proportions and associated 95% confidence intervals and compared between intervention and control groups to check the integrity of the randomisation.

Responses to the Post Appointment Questionnaire will be assumed to be additive and averaged to produce the primary outcome measure. Differences between groups will be assessed using t-test.

Changes in secondary outcome measures between baseline and 6 months will be compared between intervention and control groups to identify any clinically and statistically significant differences using ANCOVA regression with patients results at baseline fitted as a covariate. The model residuals will be checked to look for outliers and bi-modality. Leave-one-out sensitivity analyses will be used to look for patients that strongly influence the results.

Two-by-two tables will be created of the predicted and observed PICS, together with statistics on sensitivity, specificity, and negative and positive predictive value. Models will be checked for influential observations and outliers. The results will be reported using the EQUATOR TRIPOD checklist to ensure completeness and transparency[29].

The overall characteristics of the sample will be described using summary statistics. This will help inform the generalisability of our results. The number of patients approached and consented will be tabulated, together with the number who dropped out or died.

.

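### The 6-month comparison in a 15-per-arm feasibility pilot is aimed at statistical significance, which would often miss an MCID-sized effect on HADS or PCL-5; it should be an exploratory estimate with confidence intervals

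*Protocol*

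**What the plan says.** The primary objective (Protocol, Aims and objectives) is "To evaluate feasibility (cost and practicability) and acceptability of an early psychiatric intervention in a post-ICU clinic". Symptom change, self-efficacy, service access, work, income and daily living are secondary.

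Under Participants and sample calculation the size is about 30 patients, "with 15 randomised to the control and intervention arms respectively". No alpha, power, SD or target difference accompanies it. The MCID table that follows lists "Anxiety/Depression HADS* ≥ 2.5 points", 10 points for PCL-5 and 0.5 for EQ-5D, but does not link them to the sample size.

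Statistical analysis then specifies ANCOVA with the baseline value as covariate for the secondary outcomes, with the stated purpose "to identify any clinically and statistically significant differences". The primary score, an average of the Post Appointment Questionnaire items, is compared by t-test. That section mentions 95% confidence intervals only for the baseline description. It does not call the between-group comparisons exploratory, and it does not say how a non-significant result will be read.

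**The concern.** The stated purpose asks more of the data than the design was built to give. If significance is the yardstick in a trial this small, two errors follow. A worthwhile effect on anxiety, depression or PTSD symptoms may be reported as no significant difference although the data do not exclude it. An effect that does cross the threshold will, on average, be too large. Both matter because Dissemination and outcome says the results are to inform later studies and further development of the intervention. Testing several outcomes at 5% also makes a chance finding more likely.

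The point is about the purpose written into the analysis. It does not call for more patients.

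**Working it through.** There is no power figure in the Protocol to reproduce, so the check asks what the stated size delivers for the stated MCIDs.

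**From the Protocol:** n = 15 per arm, 1:1 allocation; MCIDs of 2.5 (HADS), 10 (PCL-5) and 0.5 (EQ-5D); ANCOVA on baseline.

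**Assumed, because not stated:** two-sided alpha 0.05; HADS 2.5 applies to a subscale, SD 4 to 5, baseline-to-6-month correlation r 0.4 to 0.7; PCL-5 SD 15 to 20, r 0.5 to 0.7; EQ-5D 0.5 is an index value, SD 0.2 to 0.4; 12 per arm if 20% are lost.

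**Formulas:** SE = SD × √(1 − r²) × √(2/n), with df = 2n − 3. Smallest significant difference = t(0.975, df) × SE, where t is 2.052 at n = 15 and 2.080 at n = 12. Power comes from the noncentral t distribution with noncentrality MCID/SE. Exaggeration is the mean absolute estimate among significant results divided by the true effect, by simulation.

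**HADS mid case (SD 4.5, r 0.5):**
- n = 15: SE = 4.5 × 0.866 × 0.365 = 1.42; smallest significant difference 2.052 × 1.42 = 2.92; noncentrality 2.5/1.42 = 1.76; power 40%; exaggeration 1.53.
- n = 12: SE = 4.5 × 0.866 × 0.408 = 1.59; smallest significant difference 3.31; power 32%.

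**PCL-5 mid case (SD 18, r 0.5):** 10/18 equals 2.5/4.5, so power is the same: 40% at n = 15 and 32% at n = 12. The smallest significant difference at n = 15 is 11.7.

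**Ranges, for a true effect equal to the MCID:**

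| Measure | n per arm | Smallest significant difference | Power | Mean exaggeration |
|---|---|---|---|---|
| HADS 2.5 | 15 | 2.1 to 3.4 | 30% to 64% | 1.24 to 1.75 |
| HADS 2.5 | 12 | 2.4 to 3.9 | 25% to 53% | 1.33 to 1.91 |
| PCL-5 10 | 15 | 8.0 to 13.0 | 33% to 69% | 1.19 to 1.67 |
| PCL-5 10 | 12 | 9.1 to 14.7 | 27% to 59% | 1.28 to 1.82 |

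The smallest significant difference is also the expected half-width of the 95% interval. For HADS and PCL-5 it is about as large as the MCID, so a non-significant result would usually leave an MCID-sized effect inside the interval.

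**Where power passes 50% at 15 per arm:** HADS SD below about 3.9 at r 0.5, or 4.7 at r 0.7; PCL-5 SD below about 15.6 at r 0.5, or 18.9 at r 0.7.

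**EQ-5D 0.5:** at 15 per arm, even with r = 0, power is 91% (SD 0.4) to over 99% (SD 0.2), with exaggeration of at most 1.05.

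**Multiplicity:** the number of tests is not stated. Five is a count of the main scales (two HADS subscales, PCL-5, EQ-5D, self-efficacy). Eight is a count of the topics in the secondary objectives. For independent tests, 1 − 0.95⁵ = 23% and 1 − 0.95⁸ = 34%. At an assumed pairwise correlation of 0.5 the figures fall to about 18% and 25%.

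**The case against.** The strongest reply is that the damage depends on inputs the Protocol does not give. That stands. A reader might infer that the test would miss most MCID-sized effects. The ranges straddle 50%, and a somewhat smaller SD or stronger baseline correlation takes power above it, so only *often* is supported. The inference also fails for EQ-5D on an index scale.

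A reader might also infer that every significant estimate will be too large. That is true only on average: with HADS SD 4 and r 0.7, about 22% of significant estimates fall below the true effect. The 23% to 34% false-positive figures are upper ones, since scales answered by the same patients are unlikely to be independent.

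Nor does the Protocol say that a non-significant outcome will be dropped, or that a later trial will be sized on a significant one. Those are risks of how the results may be used, not stated rules. The purpose clause names clinical as well as statistical significance, and confidence intervals are not excluded: ANCOVA produces them, and a statistical analysis plan that is not shown may require them.

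What the reply does not remove is the stated purpose. It is fixed in the Protocol, it sits beside a feasibility objective and a sample size without a power basis, and nothing in the Protocol tempers it. Barring all hypothesis tests would go further than needed; labelling them exploratory is enough.

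**Conclusion.** The concern holds for HADS and PCL-5, the measures that carry the symptom-severity objective. Under the assumptions listed, an MCID-sized effect would be detected with 30% to 64% power (HADS) and 33% to 69% (PCL-5) at 15 per arm. Both are about 40% in the mid case, or about 32% with 12 per arm. At 15 per arm, significant estimates would overstate such an effect by about 1.2- to 1.75-fold on average. The chance of at least one false positive across five to eight tests is at most about 23% to 34%. It does not hold for EQ-5D if 0.5 is an index value.

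The pilot remains valid for feasibility and acceptability. The wording should be changed because it sets an inferential aim that the design cannot reliably meet.

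**What to change.** In Statistical analysis, replace the purpose clause for the secondary outcomes with text such as:

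> Baseline-adjusted mean differences (ANCOVA) will be reported with 95% confidence intervals. Where the MCID table gives a value, the interval will be read against it, stating whether it excludes, includes or exceeds the MCID. These comparisons are exploratory; no conclusion on efficacy or lack of efficacy will be drawn from p-values. SDs and baseline-outcome correlations will be reported for planning.

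Two additions keep the section consistent:
- Report the primary Post Appointment Questionnaire comparison as a mean difference with a 95% confidence interval as well.
- Report outcomes collected only at follow-up, such as Health Services Use, as unadjusted differences with intervals, since they have no baseline to adjust for. Outcomes without a listed MCID, such as self-efficacy and employment, get the interval alone.

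Keep the ANCOVA, the residual checks and the leave-one-out analyses. The cost is a few sentences, with the same data and model and no extra patients. What is given up is a claim of statistical significance on the secondary outcomes.

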# Study plan / participants and recruitment

**Study design:**

This pilot study is a prospective, single site, parallel randomised controlled trial. Data will be collected with consent from routinely kept hospital records, and from participants at two times as specified below.

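### The protocol commits a randomised pilot trial to a PICS-prediction analysis and TRIPOD reporting that serve none of its objectives, with no designated predictor and no yes/no rule for PICS

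*Protocol*

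**What the plan says.** After the t-test for the primary outcome and the ANCOVA for the secondary outcomes, the Protocol's *Statistical analysis* section adds a separate paragraph: "Two-by-two tables will be created of the predicted and observed PICS, together with statistics on sensitivity, specificity, and negative and positive predictive value". That paragraph goes on to mention checking models for influential observations and outliers, and closes: "The results will be reported using the EQUATOR TRIPOD checklist to ensure completeness and transparency".

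The *Study design* section says: "This pilot study is a prospective, single site, parallel randomised controlled trial". *Participants and sample calculation* sets the sample at "approximately 30 patients attending the Redcliffe ICU follow-up clinic over a 12-month period, with 15 randomised to the control and intervention arms respectively".

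The *Aims and objectives* section gives one primary objective, "To evaluate feasibility (cost and practicability) and acceptability of an early psychiatric intervention in a post-ICU clinic", and three secondary ones. The first is "Assess the impact of early psychiatric assessment and provision of referral options on self-efficacy and rates of health service access" (in patients who need psychological care). The second is "Measure the change in symptom severity for anxiety, depression, and PTSD between presentation, and 6 months after presentation". The third concerns effects on employment, income and independence in daily activities.

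**The concern.** The accuracy paragraph reads as if it belongs to a prognostic study. It presupposes three things: a rule or model that predicts PICS, a binary PICS outcome to compare it with, and a question about prediction that the trial wants answered. The objectives contain no such question, and the protocol fixes neither of the other two.

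Left as it is, the paragraph cannot be carried out as written. Or it is carried out with a predictor, threshold and case definition chosen after the data are seen, in about 30 patients of whom half have had the study intervention. Either way, accuracy figures could be published that the trial was not designed to produce. The one reporting checklist named is also for a kind of study that this is not.

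**Working it through.** The protocol gives no figure for the precision or size of this analysis, so there is nothing to reproduce. The check sets sections side by side. The arithmetic after it is illustrative only.

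**1. Is there an objective?** The four objectives cover feasibility and acceptability, self-efficacy and service access, symptom change, and work, income and daily living. None asks how well anything predicts or classifies PICS.

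**2. Is there a predicted PICS?** No section names a prediction model, an index test or a threshold. *Background information* collects questionnaires on risk and protective factors. Among them is the PAS, a 10-item screen for risk of PTSD and/or depression after traumatic injury. It is the nearest candidate, but it has no stated cut-off, targets narrower outcomes than PICS, and is not mentioned in *Statistical analysis*.

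**3. Is there an observed PICS?** *Background and rationale* describes PICS as a concept. The table of PICS features gives minimally important differences for HADS, PCL-5 and EQ5D. Those are thresholds for change, not a rule for who has PICS. *PICS Measures* gives one score cut-off (HADS subscale above 7) without tying it to PICS status. There is no cut-off for PCL-5 or EQ-5D-5L, no rule for combining measures, and no stated time point for PICS status.

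**4. Does the design suit it?** Allocation is 1:1, so about half the sample receives an intervention which *Background and rationale* hopes will lower the long-term burden of PICS. Under *General Assessment*, the psychiatrist reads the baseline questionnaire results before seeing an intervention participant. In that arm, a baseline predictor would therefore help to guide the care that is meant to change the outcome. The accuracy paragraph does not say how arm is handled.

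**5. How precise could it be?**

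- From the protocol: N about 30. Prevalences of 46% (anxiety), 40% (depression) and 22% (PTSD), and up to 80% for any post-ICU complication, all from *Background and rationale*.
- Assumed: one of these prevalences applies to the outcome; sensitivity and specificity are near 80%; no loss to follow-up.
- Cases n = 30 × prevalence, rounded. Correctly classified x = 0.8 × n, rounded; likewise for non-cases.
- Exact (Clopper–Pearson) 95% limits: lower = 2.5% quantile of Beta(x, n − x + 1); upper = 97.5% quantile of Beta(x + 1, n − x).

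| Prevalence | Cases / non-cases | Sensitivity (95% CI) | Specificity (95% CI) |
|---|---|---|---|
| 22% | 7 / 23 | 6/7 (42–100%) | 18/23 (56–93%) |
| 40% | 12 / 18 | 10/12 (52–98%) | 14/18 (52–94%) |
| 46% | 14 / 16 | 11/14 (49–95%) | 13/16 (54–96%) |
| 80% | 24 / 6 | 19/24 (58–93%) | 5/6 (36–100%) |

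The sensitivity interval is 100 − 42 = 58 points wide at 22% prevalence and still 93 − 58 = 35 points wide at 80%. If 6 of the 30 were lost (an assumed 20%), 22% prevalence leaves 24 × 0.22 ≈ 5 cases, and 4/5 has an interval of 28–99%. Splitting by arm to avoid mixing in the treatment effect leaves 15 × 0.22 ≈ 3 to 15 × 0.80 = 12 cases per arm, if prevalence is equal in both.

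**The case against.** Much can fairly be said for the plan.

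- **Detail can sit in an SAP.** The predictor, cut-off, case rule and handling of arm are often settled there, and one may exist that is not shown. This stands: missing detail alone would not be a finding. But an SAP cannot make the analysis serve an objective the protocol does not have, and the protocol itself fixes the analysis and the checklist.
- **A reader might infer that observed PICS cannot be constructed, because the 6-month survey has no cognitive test.** The documents do not support this. *Background and rationale* lets the impairments count singly as well as together, so a psychological or physical impairment alone could qualify. HADS, PCL-5 and EQ-5D-5L are all repeated at 6 months. What is missing is the yes/no rule.
- **A reader might infer that the trial has no predictor and no definition of PICS at all.** That is too strong. The PAS is collected, and a conceptual definition is given. What is lacking is a designated predictor or model and an operational definition.
- **A reader might infer that the whole trial will be reported under TRIPOD.** The sentence closes the paragraph on the two-by-two tables and may refer to those results only. The following paragraph separately tabulates patients approached, consented, dropped out and died. It remains true that no other reporting checklist is named.
- **A reader might take pooling over arms as given.** The protocol does not say so. The mixing of accuracy with treatment effect is conditional on pooling.
- **The consequence is limited.** The primary t-test and the ANCOVA comparisons do not depend on this paragraph, and no decision is attached to it. This also stands.

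**Conclusion.** The concern holds as a mismatch between a stated analysis and the trial's own objectives and design. The protocol commits to accuracy statistics for PICS prediction with no matching objective, no designated predictor or model and no rule for PICS present or absent. For a parallel randomised pilot it names only a prediction-model checklist.

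That conclusion rests on comparing sections and needs no assumption. The size does: with prevalence between 22% and 80% and sensitivity near 80%, about 30 patients give exact 95% intervals for sensitivity 35 to 58 points wide, before any loss to follow-up. Other assumed values would move these figures, but not enough at this sample size to make accuracy estimates informative.

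The paragraph should be corrected before analysis. It does not threaten the primary or secondary treatment comparisons.

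**What to change.** Delete the sentence on two-by-two tables and accuracy statistics and the TRIPOD sentence. Name in their place a reporting standard for randomised pilot trials. If the sentence on checking models is meant for the ANCOVA models, move it there.

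If baseline risk is of interest, add one line: baseline PAS will be described against 6-month HADS and PCL-5 by arm, labelled exploratory, with no sensitivity, specificity or predictive-value claims. All three are already collected.

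The cost is a text edit, with no new data, visits or patients. The small downside is the loss of an exploratory accuracy table that this sample could not estimate usefully. A sponsor who wishes to keep such a table would instead need an added exploratory objective stating the predictor and cut-off, the PICS case rule and time point, and the handling of arm, with confidence intervals. The imprecision shown above would remain.

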# Ethical Considerations

Ethical issues relevant to the study and procedures to promote best practice are outlined below.

All participants will be made aware that any participation is completely voluntary.

**Consent:**

All potential participants will receive information about the study in writing and verbally and have the opportunity to ask any questions they have and discuss their participation with a person of their choosing should they wish. Potential Participants will be allowed as much time as they need to consider participation, and participants can decline assessments or withdraw from further participation at any time.

The research team decided for simple randomisation prior to consent for the following reasons:

Minimise departure from standard practice for participants not participating in the study.

In BAU, patients are not invited to the post-ICU clinic while still in ICU, and this is instead discussed several weeks after discharge to allow some time for rest and recovery prior. Informed consent while still in hospital would require participants to make a decision about the post-ICU clinic much earlier in their recovery trajectory than usual.

Respect the patient’s right to distributive justice

The research team were concerned that because ICU clinical staff cannot be blinded to when the intervention is available, a non-structured approach to appointment allocation risks unconscious bias from staff. While a departure from BAU, simple randomisation would ensure that patients’ rights to equal opportunity in care and to participate in research is respected.

Respect the patient’s right to sufficient opportunity to consider participation prior to consent

In BAU, participants are invited to attend the post-ICU clinic via telephone several weeks after discharge. The research team felt that invitation to participate, or even to randomisation in this setting would not provide the patient sufficient time to reflect and seek advice before making a decision.

**Confidentiality and privacy:**

First approach to patients regarding the study will be by a member of the treating team who will seek permission to introduce a researcher.

Data will be de-identified at source and stored using research code numbers. Information linking named participants to these code numbers will be kept separately from any research databases and archived for fifteen years once data collection has been completed.

**Participant safety:**

The study will be conducted in accord with the principles of the Helsinki Declaration and International, Australian and Queensland legislation and Queensland Health policies and procedures. Full ethical approval will be sought prior to collection or analysis of research specific data. Ethical approval will be sought from the RBWH Human Research Ethics Committee, and Research Governance approval will subsequently be applied for.

However, all participants will be provided with contact details for services where they can seek support if required. If we identify an acute deterioration in mental state or imminent risk, the participant will be directed to attend the local hospital for review by the relevant mental health service, as described in the study procedure.

We are aware of the potential for some people who agree to contact at either time point to have become unwell or die before the next contact. In all cases, follow-up contact will be handled sensitively.

# Dissemination and outcome

Results will be published in peer reviewed publications and presented at professional conferences. Results will also be presented to local decision makers and in appropriate local consumer forums.

Participants will be asked if they wish to receive plain English summaries of the results from the study. Plain English summaries will be posted to interested participants.

As there is a paucity of evidence in this area, the results of this study will inform future studies seeking to estimate the burden of disease of PICS in Metro North HHS and continue to develop a targeted intervention for PICS applicable to both Metro North hospitals, nationally and internationally.

